## Abstract

**Background:**

The COVID-19 pandemic has increased the level of anxiety among Indonesian senior high school teachers, who face challenges to treat their mental disorder symptoms that arise during their working hours, as mental health services in Indonesia are limited. Therefore, it is vital to equip schoolteachers in Indonesia with early interventions that are easily available, private, and affordable, and 1 feasible approach is to deploy a smartphone mobile app.

**Objective:**

The objectives of this study are (1) to evaluate the feasibility of a brief mindfulness–based mobile app (BM-MA) for Indonesian senior high school teachers experiencing anxiety and stress and (2) to examine the effects of using the BM-MA on anxiety, stress, life satisfaction, self-efficacy, trait mindfulness, self-compassion, and physical and social dysfunction among the participants.

**Methods:**

We followed the SPIRIT (Standard Protocol Items: Recommendations for Interventional Trials) 2013 statement for this feasibility randomized controlled trial (RCT) protocol. A total of 60 Indonesian senior high school teachers were recruited for this study and randomly assigned to either the intervention group (BM-MA) or a wait-list control group (CG) in a 1:1 ratio. The BM-MA group was required to engage in mindfulness practices using the app for 10-20 minutes per day for 3 weeks. All participants were assessed with a battery of self-report measures at baseline, postintervention, and at 1-month follow-up. Validated scales used to measure the outcome variables of interest included the Satisfaction With Life Scale (SLS), the Teachers’ Sense of Efficacy Scale (TSES), the Self-Compassion Scale—Short Form (SCS-SF), Generalized Anxiety Disorder-7 (GAD-7), General Health Questionnaire-12 (GHQ-12), and the Five Facet Mindfulness Questionnaire (FFMQ). The practicality and acceptability of the app will be evaluated using the Client Satisfaction Questionnaire-8 (CSQ-8) and structured qualitative interviews. Data from the interviews will be analyzed with the deductive thematic analysis framework as a process of qualitative inquiry. Repeated measures ANOVA with groups (intervention vs control) as a between-subject factor and time as a within-subject factor (baseline, postintervention, and 1-month follow-up) will be used to examine the effects of the BM-MA on the outcome variables. The data will be analyzed using an intent-to-treat approach and published in accordance with CONSORT (Consolidated Standards of Reporting Trials) recommendations.

**Results:**

Participants were recruited in December 2023, and this pilot RCT was conducted from January through March 2024. Data analysis was conducted from March through May 2024. The results of this study are expected to be published in December 2024. The trial registration of this protocol was submitted to the Chinese Clinical Trial Registry.

**Conclusions:**

This study aims to determine the feasibility and efficacy of the BM-MA, a digital mental health intervention developed using an existing mindfulness-based app, and assess its potential for widespread use.

**Trial Registration:**

Chinese Clinical Trial Registry ChiCTR2300068085; https://tinyurl.com/2d2x4bxk

**International Registered Report Identifier (IRRID):**

DERR1-10.2196/56693

## Introduction

### Background

During the COVID-19 epidemic, 79.1% of government senior high school teachers in Jakarta, Indonesia, experienced stress due to workload, work engagement, work routine, and the workplace environment [1]. The higher stress level of schoolteachers during the pandemic was closely tied to the increased workload caused by a shift in the teaching format [2]. The educational strategy during the COVID-19 pandemic was ambiguous, leading to differences in how teaching was implemented. Teachers often interpreted the policy based on their existing knowledge and teaching skills [3]. Another ambiguity in the online school period was that teachers perceived a lack of explicit consequences, whether positive or negative, for the quality of their online teaching delivery [3,4].

Teachers between the ages of 36 and 45 years were found to experience greater levels of stress and anxiety than older teachers, since younger teachers were required to perform more technology-related duties that the older teachers could not perform [5]. Malini [5] also reported that schoolteachers lack a means of coping with their mental health. The condition of schoolteachers does not improve, and they receive less assistance in managing stress and depression. After 2 years of the pandemic, Indonesian senior high school teachers reported elevated levels of anxiety and somatic and social dysfunction [6].

In general, mental health services in Indonesia are limited, with psychologists, psychiatrists, and therapists being more accessible in major cities and not covered by national insurance [1-3]. There are significant disparities in the level of mental health literacy among those engaged in the health care system throughout various regions of Indonesia. The guidelines and allocation of support for mental health practitioners still present unresolved concerns. In certain regions of Indonesia, accessing the nearest community health clinics for mental health services can be challenging and costly due to a lack of competent and knowledgeable human resources in this field [7]. As a result, Indonesian senior high school teachers face challenges to treat the symptoms of mental disorders that arise during their working hours, because there are few public hospitals that have a psychology/psychiatry department [6,7]. Teachers can also get professional mental health services at a private hospital. However, private hospitals charge 4 times more than public hospitals for 1 psychotherapy season [6,7].

In view of the aforementioned circumstances, it is vital to equip schoolteachers in Indonesia with early interventions that are easily available, private, and affordable, and 1 feasible approach is to deploy a smartphone mobile app. A smartphone has multiple capabilities, such as presenting on-demand video resources and opportunities for live engagement with users. Consequently, it can be used to provide schoolteachers with accessible, inexpensive, and extended psychological interventions. Research has found that individuals with stress management skills and favorable living conditions are likely to have more long-term happiness [8]. Mindfulness-based interventions are 1 category of interventions that may be effective in improving well-being and stress management skills [9]. One popular mindfulness-based intervention is “Mindfulness-Based Stress Reduction” (MBSR). The MBSR was originally developed to address a variety of diseases in clinical and nonclinical populations. The program consists of 8 weekly sessions, plus approximately 45 minutes of daily home practice [10].

Much research has examined the effectiveness of the MBSR and other forms of mindfulness meditation in addressing mental health symptoms. Studies have revealed that the effect sizes for the MBSR are larger than those for other kinds of mindfulness meditation, likely due to the fact that the MBSR uses a variety of processes, such as formal meditation practices and live instruction by a trained facilitator [10-12]. Several studies have demonstrated the efficacy of mindfulness interventions for schoolteachers’ stress and anxiety [13-18], as well as stress related to COVID-19 [16]. However, relatively few studies have examined the effects of mindfulness training–based mobile apps for schoolteachers. One of the few empirical studies examined the effects of a 5-week standardized meditation program consisting of weekly offline classes and a suggested dose of 2 daily 20-minute home and school practice sessions [17]. The types of meditation practices included in this intervention included mantras and breath observation. The sample consisted of elementary, middle, and high school teachers who were randomly allocated to intervention (n=45) and control (n=46) groups. Findings indicated improvements in state and trait anxiety, reduction in emotional weariness (a component of burnout), and reduction in stress posttest, and lowered depersonalization (another component of burnout) at 1-month follow-up. Another study of the MBSR for primary school teachers [19] showed improvements in melancholy and stress, as well as increased tolerance and lowered prejudice (a component of the mindfulness scale) among schoolteachers following engagement in the intervention.

This feasibility study comprises 3 weeks of daily use of a mobile phone app. The lessons are organized based on components of the MBSR, and mobile apps are used to provide instructions for exercises requiring 10-20 minutes of daily home practice. Existing mindfulness interventions for general populations based on mobile apps for smartphones are primarily given in English, with rating stars based on user reviews [20]. There have been studies on the efficacy of mindfulness-based mobile apps in broad populations [20-22]. Several studies based in Iran have suggested the use of online and digital mindfulness programs as an efficient method to alleviate the stress related to COVID-19 and enhance psychological resilience [23]. To summarize, mindfulness-based mobile interventions have been demonstrated to be effective in reducing stress and enhancing well-being in a variety of settings [10,22,24].

To date, mobile app–based mindfulness interventions have not yet been implemented in the Indonesian language for senior high school teachers. According to the 2019 Global Economy Survey [5,6], which ranked Indonesia 72nd out of 97 countries in terms of the senior high school teacher-student ratio, there appears to be a decline in teacher supervision and student attention. As a result, schoolteachers are facing increased workloads, leading to higher levels of stress and physical complaints [4]. To support Indonesian senior high school teachers in managing anxiety and stress symptoms effectively and in a user-friendly manner, it is crucial to develop a brief mindfulness–based mobile app (BM-MA) intervention in Indonesia. Since such an app has not yet been implemented in Indonesia, this study aims to assess the feasibility and acceptability of the BM-MA to determine its suitability for further testing through a randomized controlled trial (RCT) [25].

### Study Objectives

This feasibility study will evaluate the possible adoption of the BM-MA in real-world contexts. The secondary objectives are to determine the effectiveness of BM interventions based on mobile apps in enhancing life satisfaction, self-compassion, and a sense of self-efficacy and in reducing participant-reported anxiety and stress symptoms. The following scientific questions will be addressed:

Can the BM-MA be accepted into the community practice of Indonesian senior high school teachers to enable scale-up?Throughout the study, could the BM-MA be applied as intended?Could the BM-MA implementation be continued throughout the conclusion of the research?Does the BM-MA reduce stress and promote life satisfaction, self-compassion, and a sense of self-efficacy, as stated by participants?Does the BM-MA reduce participant-reported anxiety symptoms?

## Methods

### Overview of Study Design

This feasibility study will use a repeated-measures, between-group RCT design and adhere to the CONSORT (Consolidated Standards of Reporting Trials) statement (Multimedia Appendix 1). The feasibility protocol presented followed the SPIRIT (Standard Protocol Items: Recommendations for Interventional Trials) 2013 statement (Multimedia Appendix 2) [26]. As determined by an initial screening instrument, participants were only recruited if they exhibited good overall health, had no past experience with mindfulness practice, and had not recently experienced any adverse life events. Individuals who matched the inclusion criteria (explained further in the subsequent section) and responded within the recommended time frame of 2 weeks were routed to a webpage and a participant information sheet via the Qualtrics platform. Participants from 2 public senior high schools were informed that they would be randomly assigned to a treatment group or a wait-list control group (CG) and were asked to provide written informed consent (see Multimedia Appendix 3) prior to completing a brief demographic questionnaire. The participants were subsequently randomly assigned to either the BM-MA group or the CG. Participants in the CG were notified that they were on a waiting list and were asked to answer questionnaires at baseline, postintervention, and at 1-month follow-up before being allowed access to the BM-MA intervention for an additional 21 days (if they wished to use it).

At the end of the waiting period, the CG received thorough instructions regarding downloading and using the BM-MA intervention via a smartphone. In the meantime, the BM-MA group was instructed to complete questionnaires at baseline, postintervention, and at 1-month follow-up of the BM-MA intervention. After the baseline measures were completed, participants in the BM-MA group were provided with an access code and details of how to download the BM-MA to their smartphone. During the 21-day study period, they were urged to use the app daily. At baseline, postintervention, and at 1 month follow up of the BM-MA intervention, both groups were invited to attend a Zoom session to finish the measurements in real time, monitored by random assignments. Both groups were reminded about their right to withdraw from the study at any moment if they so chose. The follow-up evaluation was conducted 1 month postintervention for both groups. The intervention tries to ensure that no participant will face stigma as a result of participation by removing any potentially objectionable language according to the feedback from the local government partner, the Dinas Pendidikan Kepemudaan dan Olahraga Provinsi (Province Youth and Sports Office). The overview of the BM-MA pilot RCT study design following CONSORT guidelines is presented in Multimedia Appendix 1.

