#### Sociodemographic and Personal Information

During the screening session, participants’ sociodemographic and personal information was collected using a combination of questions. The open questions inquired about participant age, years as a teacher, and salary, whereas the closed questions required participants to select from a list of options, such as the education level and internet access on a smartphone (yes/no). To ensure participants’ eligibility, sociodemographic and personal data were requested once again at baseline.

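### As the article describes it, the baseline scales come after randomisation and after controls learn they are wait-listed, so Day 1 scores may already carry a reaction to allocation

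*Protocol article*

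**What the plan says.** The order of events has to be read from the narrative in Overview of Study Design.

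- Before allocation, participants from the two schools "were asked to provide written informed consent (see Multimedia Appendix 3) prior to completing a brief demographic questionnaire". No outcome scale is mentioned at this step.
- Next: "The participants were subsequently randomly assigned to either the BM-MA group or the CG".
- Then, for controls: "Participants in the CG were notified that they were on a waiting list and were asked to answer questionnaires at baseline". The sentence goes on to list the two later assessments.
- For the app arm: "the BM-MA group was instructed to complete questionnaires at baseline, postintervention, and at 1-month follow-up of the BM-MA intervention".
- At each assessment, baseline included, "both groups were invited to attend a Zoom session to finish the measurements in real time, monitored by random assignments".
- App access comes last: "After the baseline measures were completed, participants in the BM-MA group were provided with an access code".

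Randomization and Blinding says that neither the assignment nor the outcome evaluation can be blinded. The Abstract describes the outcome battery as self-report. Data Analyses names a repeated-measures ANOVA with baseline, day 21 and day 41 as time levels, and a Cohen d built on variation from baseline. Table 1 shows GAD-7 and GHQ-12 at screening as well as at baseline. PSS, SLS, SCS-SF, TSES and FFMQ are first measured at baseline.

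**The concern.** Randomisation balances the arms, in expectation, on whatever is measured before allocation is known. On the order described, Day 1 precedes use of the app but not knowledge of the arm. Self-reported anxiety, stress, self-efficacy and life satisfaction can respond to being told to wait, or to expecting help soon. Day 1 would then not be a clean pre-treatment value, and any estimate measured from it could carry an allocation reaction of unknown size and sign. The secondary effect estimates are at stake. The Discussion says the findings will decide whether efficacy testing is recommended.

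**Working it through.** **Order of procedures.** The text contains no figure to reproduce, so the first check is the sequence: consent, demographic form, assignment, wait-list notice, baseline scales with both arms already named as groups, access code. Nothing in the article puts the outcome battery before assignment.

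**Size, under assumptions.** Take 30 per arm (Recruitment and Sample Size), equal SDs, no true effect and a normal approximation. The documents give neither the shift nor the correlation, so I assume a Day 1 difference between arms of s = 0.1 to 0.3 SD and a Day 1 to follow-up correlation of r = 0.5 to 0.7.

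Standard errors in SD units, with sqrt(2/30) = 0.258:

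- Change score: sqrt(2(1 − r)) × 0.258 = 0.258 at r = 0.5 and 0.200 at r = 0.7.
- ANCOVA on Day 1: sqrt(1 − r²) × 0.258 = 0.224 at r = 0.5 and 0.184 at r = 0.7.

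If the reaction affects Day 1 and has gone by Days 21 and 41, the bias is s for change and r × s for ANCOVA. The rejection rates below are for a two-sided 5% test, at r = 0.5 to r = 0.7.

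| s (assumed) | Change: bias | Change: rejection | ANCOVA: bias | ANCOVA: rejection |
|---|---|---|---|---|
| 0.1 | 0.1 | 6.7% to 7.9% | 0.05 to 0.07 | 5.6% to 6.7% |
| 0.2 | 0.2 | 12.1% to 17.0% | 0.10 to 0.14 | 7.3% to 11.8% |
| 0.3 | 0.3 | 21.3% to 32.3% | 0.15 to 0.21 | 10.3% to 20.7% |

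At r = 0.5 the top of the range is 0.3/0.258 = 1.16 standard errors for change, but only 0.15/0.224 = 0.67 for ANCOVA. For scale, the 95% half-width for a standardised difference in a single score is 1.96 × 0.258 = 0.51.

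**Persistence.** If a fraction k of the reaction remains at the later visit, the bias in change is s(1 − k): the full s at k = 0, half of it at k = 0.5, and zero at k = 1.

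**Direction.** On a distress scale, suppose disappointment raises the controls' Day 1 score by s and then fades. Change in controls is −s and in the app arm 0, so app minus control is +s and the app looks worse. Suppose instead that expectation lowers the app arm's Day 1 score by s and then fades. Change in the app arm is +s and in controls 0, which again gives +s. Both mechanisms hide a benefit, so the excess rejections in the table would fall mainly on the side where the app looks worse.

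**The case against.** The strongest objection is that the order is inferred. No sentence dates assignment or disclosure against Day 1. The sentence about controls lists their whole schedule and joins it to the wait-list notice with a plain conjunction. Some text would fit baseline first: for the purpose of ensuring eligibility, "sociodemographic and personal data were requested once again at baseline", which makes most sense before allocation, and Table 1 lists demographics at baseline too. The flow diagram is not in the text at hand. This stands as a limit on certainty. It does not remove the point: if baseline did come first, the Overview misdescribes the trial and needs correcting.

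Four stronger readings are tempting but not supported.

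- A reader might infer that the shift passes one for one into every analysis from baseline. That holds only for change-based estimates, and only if the reaction has gone by the later visits.
- A reader might infer that it would mimic an app benefit. The two obvious mechanisms work the other way, although the net direction is not known.
- A reader might infer that the denominator of Cohen d is distorted as well. A mean shift by arm leaves the within-arm pooled SD unchanged.
- A reader might infer a conflict between the repeated eligibility data and intention-to-treat. The article gives no rule for removing anyone at that step, and Data Analyses already includes everyone randomised.

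It is also fair to say that the primary outcome, adoption measured by an engagement and experience questionnaire, is not a change from baseline. Nor are the acceptability and feasibility measures (CSQ-8, interviews, recruitment and attrition). Finally, the trial has been conducted, so its order cannot now be changed.

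**Conclusion.** The point holds on the plain reading of the Overview: Day 1 follows assignment and the wait-list notice, without blinding and with self-reported outcomes, and is then used as the baseline for the secondary efficacy estimates. These may therefore be biased by a reaction to allocation. The size is not known from the documents. An assumed 0.2 SD reaction confined to Day 1 would bias change by 0.2 SD and a Day 1 ANCOVA by 0.10 to 0.14 SD; equal persistence would bring the bias in change to zero. The conclusion rests on the narrative order being the actual order. It is worth correcting, but it concerns secondary outcomes only.

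**What to change.** 1. State the actual order of consent, baseline scales, generation of the allocation and its disclosure. This costs a sentence.
2. In the design, and so in any later trial, complete all baseline scales before allocation is generated and disclosed. This re-orders two steps and needs no new data.
3. If the data were collected in the described order, add an analysis of GAD-7 and GHQ-12 with the screening score as baseline covariate, reported next to the Day 1 analysis. Both scores were used for entry, so they precede allocation. Because the Results section says that analysis ran from March through May 2024, label this as an added analysis.
4. For PSS, SLS, SCS-SF, TSES and FFMQ, which have no earlier value, state the limitation.

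The downside is small. Screening scores are older and are range-restricted by the entry caps (no more than 14 on GAD-7 and 20 on GHQ-12), so they will correlate less with the outcome and gain less precision. They remove the contamination of Day 1 but not a reaction still present at Days 21 and 41, which is why the two analyses belong side by side.

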### Timeline and Study Setting

This feasibility study was conducted among schoolteachers from 2 public senior high schools in Indonesia over a 21-day period (Multimedia Appendix 4). A total of 30 participants per group (BM-MA and control) were adequate to establish feasibility [27]. A demographic survey of senior high school teachers in Indonesia [4] revealed that the median monthly pay for schoolteachers was IDR 5,000,000 (~US $321). Almost all the participants have a smartphone (n=55, 91.7%) and internet access on their smartphone (n=60, 100%), and only 17 (28%) said they had no intention of obtaining mental health treatment. To the best of our knowledge, there has been no formal record of senior high school teachers in Indonesia using mental health treatments. Nevertheless, the remarkable progress of Indonesia’s mental health care system is still restricted to a few major cities on Java Island [7].

### Local Stakeholder Partner

This study will be conducted in partnership with local education authorities in a number of Indonesian provinces, specifically the Dinas Pendidikan Kepemudaan dan Olahraga Provinsi (Province Youth and Sports Office). The government education authorities are responsible for the following:

The creation of education-related technological policyThe implementation of educational policy and the growth of language, literacy, and literatureEducation administration in the realm of educationImplementation of program planning, assessment, and reportingThe execution of other functions assigned by the governor that are linked to their duties and responsibilities

On the basis of the aforementioned capabilities, the local government partners made a major contribution to recruiting participants to take part in this feasibility study by sending invitations over email to prospective participants.

